### Limitations

The primary end-point is 30-day mortality which is associated with multiple factors besides the triage model used at admission. Mortality has been used previously to assess the efficacy of triage models [19, 21–23]. If CTA has any impact on acute mortality (e.g. 8 h) it would also affect 30-day mortality given it is the only intervention performed. However, if 8-h mortality was chosen as primary end-point, it would favor a model ranking a majority of patients in acute category and not necessarily reflect the impact on less acute patients who might die during hospitalization or within the first month. Admission to ICU as secondary endpoint was chosen to reflect a more immediate impact of triage.

In the acute care setting, it is not feasible to randomize individual patients for different triage models for several reasons. The individual randomization would be a huge logistical challenge in a busy ED and it would be

associated with delays and crowding, which would be unethical. Furthermore, it is likely that the staff would prefer the faster algorithm (CTA) and tend to use that in most patients once it is available in the department. To avoid this, cluster-randomization was chosen. Cluster-randomized design introduces dependence between individual units sampled (e.g. difference in patient population, skill of ED nurses/physicians). This is largely alleviated by cross-over in the study and relies on a similar patient inclusion during both parts of the study. This is ensured by determining the total study period through number of included patients instead of time. Furthermore, the number of clusters were very small but the cross-over design partly compensates for this.

Readmissions after 30 days are also included which means patients can be exposed to both DEPT and CTA triage during the study period. This means patients with diagnoses prone to readmission will be overrepresented in the study. Moreover, if the inclusion rate differs significantly between the two hospitals during the study period this might slightly favor the model used in most patients late in the study due to lead-time bias. It is possible for patients to be admitted in both hospitals during the study period though not likely. Patients are not systematically transferred between these two hospitals so systematic bias is unlikely in this regard. A final limitation of the study is that patients with suspected major trauma are admitted to a tertiary center in the region, meaning that few such patients will be included. However, the major aim of the CTA study is not to focus on seriously injured patients as they are managed according to specific algorithms anyway.

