## Design

The study is a prospective two-center, cluster-randomized, cross-over, non-inferiority trial. CTA is compared to the preexisting DEPT. The primary aim of the CTA is to assess if it improves patient outcome, secondarily to obtain a faster ED acuity stratification. The primary end-point is 30-day mortality and secondary end-points are length of stay (LOS), time to treatment, admission to intensive care unit (ICU), and readmission within 30 days. Follow-up information will be attained from central registries.

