## Setting and interventions

Two equally sized ED's in the capital region of Copenhagen are recruited to perform the study; Herlev Hospital and Bispebjerg Hospital with 70.000 and 85.000 annual admissions, respectively [26, 27]. Both centers are 24-h acute care hospitals offering broad medical, surgical, neurological, level-2 trauma and ICU services. The centers are randomly assigned to perform either CTA or DEPT triage as primary evaluation of patients. Subsequently, both hospitals will cross-over to use the other model. The number of admissions with CTA and DEPT will be 1:1. The CTA will be implemented during 2 weeks before initiation of data collection.

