### Sample size

The trial is designed as a non-inferiority trial, i.e. to show that 30-day mortality using CTA is not higher than using DEPT. The 30-day mortality in all admitted patients in the TRIAGE database was 4.2 % [24] and the 28-day mortality in the Acute Admission Database was 4.2 % [28]. Hence, we estimated the 30-day mortality to be 4.2 % for this study. Due to the estimated low incidence of the primary end-point, the proportional difference between the CTA and DEPT group (non-inferiority margin ( $\Delta$ )) is set at 0.5 %. The power to confirm non-inferiority is set at 80 % with a two-sided confidence interval of 95 %, which would require a sample size of 39,820. We chose to include a minimum of 40,000 patients. The combined percentage of admission to intensive or semi-intensive care unit in the TRIAGE database was 3.4 % [24], i.e. sample size should be adequate to prove non-inferiority for this secondary end-point as well. Reported 30-day readmission rate is usually around 10 % [29] meaning sample size will likely be sufficient to prove non-inferiority. In calculating the primary end-point of 30-day mortality, patients readmitted more than 30 days after discharge will be considered as separate encounters.

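### The sample size treats encounters as independent although two hospitals cross over once, so the stated power is an upper bound, and an interval computed without allowance for hospital-by-period variation would be too narrow

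*Protocol*

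**What the plan says.** Protocol, Design: "The study is a prospective two-center, cluster-randomized, cross-over, non-inferiority trial". Under Setting and interventions, "The centers are randomly assigned to perform either CTA or DEPT triage as primary evaluation of patients" and "Subsequently, both hospitals will cross-over to use the other model". The unit of randomisation is thus the hospital, with two clusters and four hospital-periods. The same section says "The number of admissions with CTA and DEPT will be 1:1".

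Under Sample size, "we estimated the 30-day mortality to be 4.2 % for this study", the margin is 0.5 % and "The power to confirm non-inferiority is set at 80" per cent with a 95 % two-sided interval. This yields 39,820, and at least 40,000 are planned. No intracluster correlation, design effect or hospital-by-period variance appears. Timeline reports about 50,000 recorded visits.

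Statistics bases the decision on a 95 % two-sided interval for the difference between the CTA and DEPT cohorts. It does not say how that interval is calculated, and names no hospital, period or cluster term.

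Limitations acknowledges that cluster randomisation makes patients dependent, then says: "This is largely alleviated by cross-over in the study and relies on a similar patient inclusion during both parts of the study". It adds that setting the study length by patient count secures this similarity, and that "the number of clusters were very small but the cross-over design partly compensates for this".

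**The concern.** Cross-over compares each hospital with itself, so a stable difference between the hospitals cancels. If the design is balanced, a change over time shared by both hospitals cancels too. What does not cancel is a change that differs between the hospitals, such as staffing, case mix or crowding shifting at one site and not the other. Fixing the number of patients equalises the size of each hospital-period, not its underlying mortality.

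The protocol's own Discussion makes such variation plausible. It cites a study with 34 % higher 10-day in-hospital mortality in overcrowded shifts. As illustration only, since the endpoint differs: 34 % of 4.2 % is about 1.43 percentage points, so a 14-point change in one hospital's share of crowded shifts would move that hospital-period's mortality by about 0.14 × 1.43 = 0.2 points.

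At stake is the primary mortality conclusion. If such variation exists and the interval ignores it, non-inferiority will be declared too often when CTA is truly worse by the full margin.

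**Working it through.** **Inputs.** From Sample size: mortality p = 0.042 in both groups, margin 0.5 percentage points (pp; read as an absolute difference), power 80 %, 95 % two-sided interval, N = 40,000. From Timeline: N about 50,000. From Setting and interventions: 1:1 allocation; equal hospital-periods of N/4 are assumed. **Assumed**, because the document gives none: s, the SD of true mortality between hospital-periods after removing stable hospital and common period effects, taken as 0 to 0.3 pp.

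**1. Reproducing the plan's figure.** Independent patients, n per group = (z_α + z_β)² × 2p(1−p)/Δ², with 2 × 0.042 × 0.958/0.005² = 3,218.88.

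- One-sided 5 %: (1.6449 + 0.8416)² × 3,218.88 = 19,901 per group, 39,802 in total, against 39,820 stated.
- Stated 95 % two-sided interval (one-sided 2.5 %): (1.9600 + 0.8416)² × 3,218.88 = 25,265 per group, 50,530 in total.

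The stated figure therefore has design effect 1 and leaves no hidden allowance for clustering. It also matches the wrong significance level, which is a separate error. The superiority power of 0.72 in Statistics likewise matches an independent two-proportion test (0.728, assuming a 0.5 pp effect and 20,000 per group).

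**2. Degrees of freedom.** There are four hospital-period means and four parameters (intercept, hospital, period, triage model), so 4 − 4 = 0 remain. The triage contrast is the hospital-by-period contrast, so the trial's own four cells cannot provide an estimate of s.

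**3. Variance.** The estimate is the average of two within-hospital differences, so each cell enters with coefficient ±1/2.

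- Binomial part: 4 × (1/4) × p(1−p)/(N/4) = 4p(1−p)/N. Its square root is 0.2006 pp at 40,000 and 0.1794 pp at 50,000.
- Hospital-by-period part: 4 × (1/4) × s² = s².
- SE² = 4p(1−p)/N + s².

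Power = Φ(0.5/SE − 1.96). One-sided error of an unadjusted interval at the margin = Φ(−1.96 × binomial SE/SE). Example, N = 40,000 and s = 0.2 pp: SE = √(0.2006² + 0.2²) = 0.2833 pp; power Φ(1.765 − 1.96) = 42 %; error Φ(−1.388) = 8.3 %.

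| s (assumed) | Design effect, 40,000 / 50,000 | Power at 95 % two-sided interval | One-sided error if unadjusted |
|---|---|---|---|
| 0 | 1 / 1 | 70 % / 80 % | 2.5 % / 2.5 % |
| 0.1 pp | 1.25 / 1.31 | 61 % / 68 % | 4.0 % / 4.3 % |
| 0.2 pp | 1.99 / 2.24 | 42 % / 46 % | 8.3 % / 9.5 % |
| 0.3 pp | 3.24 / 3.80 | 28 % / 30 % | 14 % / 16 % |

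**4. Separating the two errors.** At the one-sided 5 % level that reproduces 39,820, power at N = 40,000 is 80 %, 72 %, 55 % and 40 % for s = 0, 0.1, 0.2 and 0.3 pp. That isolates the loss due to hospital-by-period variation.

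**5. Ceiling.** As N grows, SE tends to s. Power of 80 % at the 95 % interval needs 0.5/s of at least 2.80, so above s = 0.5/2.80 = 0.18 pp no number of patients in this design reaches it.

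**The case against.** The strongest reply is that much of this is disclosed. Limitations names the dependence, calls the number of clusters very small, claims only partial compensation for that, and makes the argument depend on similar inclusion in both parts. That stands: the sentence already carries a condition. But the condition concerns who is included and how many, whereas the argument needs hospital-by-period variation in mortality to be negligible. Neither the sample size nor the power carries the caveat.

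Three stronger readings are tempting and should be resisted.

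- **That the planned interval contains only binomial variance.** Statistics does not say how the interval is computed, and a statistical analysis plan, not shown here, may specify an adjustment. The claim that it is too narrow is conditional.
- **That 80 % power would hold if hospital-by-period variation were nil.** It would not at 40,000: the zero row gives 70 %. Comparing 61 % with the stated 80 % would charge to clustering a loss of which about half comes from the significance level.
- **That even very small variation dominates the error.** At N = 40,000, s = 0.1 pp contributes 0.0100/(0.0402 + 0.0100) = 20 % of the variance. The two parts are about equal at 0.2 pp, and only beyond that does the hospital-period part dominate.

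It is also fair that inclusion ended in January 2016, so restated power changes no design decision. The practical value now lies in how the primary interval is reported.

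**Conclusion.** The point holds in this form. The 39,820 is an independent-patient calculation applied to a two-hospital, one-cross-over design, and the stated power is an upper bound. The statement that cross-over largely deals with the dependence is justified only if hospital-by-period variation in mortality is negligible, which the trial's four cells cannot show. The interval is too narrow if it is taken from the pooled cohorts without allowance and s is above zero.

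The direction is firm; the size is not, because s is assumed. For s from 0.1 to 0.3 pp, power at the stated interval falls from 70 % to between 61 % and 28 % at 40,000, and from 80 % to between 68 % and 30 % at 50,000. The error of an unadjusted interval at the margin rises from 2.5 % to between 4.0 % and 16 %. More visits do not cure this: for a given s, the unadjusted error is larger at 50,000 than at 40,000.

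The figures rest on equal hospital-periods, 4.2 % mortality in both groups and the normal approximation. They leave out any further correlation from patients counted more than once. A reader should not infer that the trial's actual power is any one of these values.

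**What to change.** 1. **Sample size:** restate power with the table above, including the s = 0 row, and say that the calculation assumes independent encounters. Correct the significance level separately: the stated 95 % two-sided interval needs about 50,530.
2. **Statistics:** report with the primary interval the largest hospital-by-period SD at which non-inferiority would still hold, using variance = binomial variance + SD². With d the observed excess mortality under CTA in pp, and d below 0.5, this is √[((0.5 − d)/1.96)² − binomial SE²]. For d = 0 it is √(0.0651 − 0.0402) = 0.16 pp at 40,000 and √(0.0651 − 0.0322) = 0.18 pp at 50,000. If the expression under the root is negative, non-inferiority already fails at SD = 0.
3. **Limitations:** reword to state the condition, namely that hospital-by-period variation in mortality is negligible and cannot be checked from the four hospital-periods.
4. **Optional:** if the central registries can identify comparable admissions, use the same two hospitals and calendar windows in non-trial years as a rough guide to a plausible SD. Each year gives one contrast with a binomial SE of about 0.2 pp at similar volumes, as large as the SD being sought, so the estimate will be imprecise and should not be treated as known.

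The cost is a less favourable power figure, one sensitivity analysis with a wider interval, and possibly one registry tabulation. No extra patients are needed.

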**Table 2** Results of the multiple logistic regression using the CTA cut-off values on the TRIAGE database

|                       | Odds ratio | p |
|-----------------------|------------|----------|
| Oxygen treatment      | 4,27       | <0,01    |
| Systolic BP < 100     | 3,28       | <0,01    |
| Heart rate > 110      | 2,14       | <0,01    |
| Respiratory rate > 22 | 2,71       | <0,01    |
| SpO2 < 94 %           | 1,67       | <0,01    |

of the primary endpoint in the CTA and DEPT cohorts does not include  $-\Delta$ . Furthermore, CTA could show superiority over DEPT; this will be considered when the lower bound of the confidence interval mentioned above exceeds 0. This analysis will only be performed if non-inferiority is confirmed. The power to demonstrate that CTA is superior will be 0.72 with a sample size of 40.000, while there will be a 5 % chance that DEPT triage is better. LOS and time-to-treatment in the two models will be log-transformed and compared using parametric tests. The patient populations included with CTA and DEPT will be compared using standard parametric tests.

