### Timeline

After a 1 week learning period for the staff, the study was initiated the 1st of March, 2015. Herlev Hospital was selected to begin with CTA, i.e. Bispebjerg Hospital continued their use of DEPT triage. This continued until the 17th of August 2015. Subsequently, the hospitals crossed-over. By the end of January 2016 the inclusion

**Table 3** Area under the curve results for the Receiver-Operating Characteristics for DEPT, CTA and a quick clinical assessment in the TRIAGE database

|                     | AUC  | Standard error |
|---------------------|------|----------------|
| CTA                 | 0735 | 0,02           |
| Clinical assessment | 0705 | 0,02           |
| DEPT                | 0605 | 0,02           |

stopped as planned. A total of approximately 50,000 patient visits have been recorded.

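### The stated CTA–DEPT comparisons name no hospital, period or patient term, and the number-based study period that the Limitations rely on does not ensure balance

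*Protocol*

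**What the plan says.** Protocol, Design: "The study is a prospective two-center, cluster-randomized, cross-over, non-inferiority trial". Two hospitals and two periods give four hospital-periods.

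Protocol, Statistics: the primary test is a two-sided 95 % confidence interval for the difference in 30-day mortality between the CTA and DEPT cohorts. For the continuous secondary outcomes, "LOS and time-to-treatment in the two models will be log-transformed and compared using parametric tests". For the populations, "The patient populations included with CTA and DEPT will be compared using standard parametric tests". No term for hospital, period or patient is named.

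Protocol, Sample size and Limitations: an admission more than 30 days after discharge counts as a new encounter, and "patients can be exposed to both DEPT and CTA triage during the study period".

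Protocol, Limitations: dependence within clusters is acknowledged. The answer given is that cross-over largely deals with it, provided inclusion is similar in both parts of the study. On that condition: "This is ensured by determining the total study period through number of included patients instead of time".

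Protocol, Timeline: inclusion began on 1 March 2015, with Herlev on CTA and Bispebjerg on DEPT. "This continued until the 17th of August 2015. Subsequently, the hospitals crossed-over". Inclusion stopped as planned by the end of January 2016, with about 50,000 visits. No count per hospital or period is given.

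Protocol, Setting and interventions: the two departments are called equally sized, yet the same sentence gives "Herlev Hospital and Bispebjerg Hospital with 70.000 and 85.000 annual admissions, respectively".

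**The concern.** Triage model was allocated by hospital and period, so these are the two factors that can be confounded with it. The text admits the dependence but answers it only through the design, and the condition on which that answer rests is not secured by the rule cited for it. A rule on the total number of patients says nothing about how each arm divides between the hospitals and periods. Nor can it make March–August patients resemble August–January patients.

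If the division within arms is uneven, part of any mortality difference between periods or hospitals is counted as an effect of triage. The margin is only 0.5 percentage points on an expected mortality of 4.2 %, so small leaks matter. A leak in CTA's favour raises the chance of a false non-inferiority claim; one against CTA costs power. Repeat encounters, within and across arms, are a further source of dependence that the stated comparisons do not address.

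**Working it through.** **1. The plan's own figure.** The protocol puts no figure on imbalance. Its sample size of 39,820 contains no design effect: the independent-patient formula at 4.2 % and a 0.5-point margin gives 39,802 at one-sided 5 %, and 50,530 at the stated two-sided 95 % interval. That mismatch is a separate matter. Here it shows only that encounters were planned as independent.

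**2. When is an unadjusted difference free of hospital and period?** Let *a* be the share of CTA encounters from Bispebjerg in period 2 (the rest are Herlev, period 1). Let *d* be the share of DEPT encounters from Herlev in period 2 (the rest are Bispebjerg, period 1). With additive effects:

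- period leak = (*a* − *d*) × (period 2 minus period 1 mortality)
- hospital leak = (*a* + *d* − 1) × (Bispebjerg minus Herlev mortality)

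Both vanish for any effect sizes only if *a* = *d* = 1/2, that is, equal hospital-periods within each arm. The arms themselves need not match in size.

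**3. Dates.** From 1 March to 16 August is 169 days. From 17 August to 31 January is 168 days, if inclusion ran to the last day of the month. The total is 337 days, or 50,000/337 = 148 visits a day on average. At that rate the 40,000 minimum in Sample size would have been reached after about 270 days, around 25 November 2015, so the minimum did not set the stop. The 50,000 in the Abstract could have.

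**4. Size under the 70:85 assumption.** With constant intake and equal periods, *a* = 85/155 = 0.548 and *d* = 70/155 = 0.452. The period leak is 15/155 = 9.7 % of the period difference, and the hospital leak is zero. At N = 50,000 (25,000 per arm), in percentage points:

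- SE with 4.2 % in both arms: 100 × √(2 × 0.042 × 0.958 / 25,000) = 0.1794
- SE at the margin (4.7 % against 4.2 %): 100 × √((0.047 × 0.953 + 0.042 × 0.958) / 25,000) = 0.1844
- false non-inferiority if the leak favours CTA: Φ(−1.96 + leak/0.1844)
- power if the leak goes against CTA: Φ((0.5 − leak)/0.1794 − 1.96)

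| Assumed period difference (points) | Leak (points) | Share of margin | False non-inferiority | Power |
|---|---|---|---|---|
| 0 | 0 | 0 % | 2.5 % | 80 % |
| 0.2 | 0.019 | 4 % | 3.2 % | 76 % |
| 0.5 | 0.048 | 10 % | 4.5 % | 71 % |
| 1.0 | 0.097 | 19 % | 7.6 % | 61 % |

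Under this split CTA has more of its visits in August–January. Higher mortality then would count against CTA, and lower mortality in its favour.

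**5. If intake differs between periods.** With a 45:55 split of visits between the periods at both hospitals and an assumed 1-point hospital difference, the hospital leak is about 0.10 points.

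**6. What adjustment costs.** On the risk-difference scale, the adjusted estimate is the average of the two within-hospital CTA–DEPT differences. With hospital-periods of 11,290 (Herlev) and 13,710 (Bispebjerg), its SE is 100 × √(¼ × 0.042 × 0.958 × (2/11,290 + 2/13,710)) = 0.1803, against 0.1794 unadjusted. Power at N = 50,000 goes from 79.6 % to 79.2 %.

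**7. What adjustment does not do.** Intercept, triage model, hospital and period are four parameters for four hospital-period means, so nothing is left to estimate random variation between hospital-periods. The documents give no correlation. If the within-period correlation exceeded the between-period one by an assumed 0.0001 (a hospital-period SD of 0.20 points), the design effect would be 1 + 12,499 × 0.0001 = 2.25, power would be 46 %, and the true one-sided error of a nominal 2.5 % test would be 9.6 %.

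**The case against.** **Silence is not a decision.** The Statistics section does not call the difference crude or unadjusted. A stratified or standardised risk difference would fit its wording, and an analysis plan that is not at hand may add the terms. This stands in part: a reader might infer that the trial ignores its design factors in every analysis, and the document does not establish that. The point survives because the Limitations raise the dependence, answer it by design alone, and state that the needed balance is ensured.

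**The dates do not refute a number-based stop.** A reader might infer from the Timeline that the number rule was not followed. The documents do not support that. The rule concerns the total study period, inclusion stopped as planned at about 50,000 visits, and the Abstract gives the same number. Near-equal period lengths are also what steady intake would produce. What remains is that the switch is given as a date, with no number rule.

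**The 70:85 ratio may not describe the study population.** These are all annual admissions. Over 337 days they come to 155,000 × 337/365, about 143,000, against about 50,000 study visits, or 35 %. Inclusion required referral to an ED bed and left out several groups. The eligible split could be equal, and the leak in step 4 would then be zero. This objection stands in full, so the figures are conditional.

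**The assumed period differences are not small.** 0.5 and 1.0 points are about 12 % and 24 % of the 4.2 % rate. At 0.2 points the leak is 4 % of the margin.

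**Conclusion.** The point holds as a modest weakness that is cheap to mend. The comparisons as stated name none of the factors by which the trial allocates, and the safeguard cited for their omission does not secure the balance that an unadjusted difference needs. Limitations and Timeline must be reconciled on how the switch and the stop were set; which account is right cannot be decided from the document.

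Under the 70:85 split the leak is 0.019 to 0.097 percentage points for assumed period differences of 0.2 to 1.0 points, or 4 % to 19 % of the margin. Both the split and the period difference are assumptions. The effect of repeat encounters cannot be sized, because their number is not given.

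A reader might also infer that hospital and period terms with patient-clustered variance make the interval valid for the cluster design. They do not: they remove fixed hospital and period effects and allow for repeat patients, but random variation between the four hospital-periods stays outside the interval and could be the larger problem.

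**What to change.** - Primary analysis: estimate the CTA–DEPT risk difference for 30-day mortality, with 95 % CI, from a model with triage model, hospital and period as fixed effects and patient-clustered robust variance.
- Use the same terms for log LOS, log time to treatment, ICU admission and readmission.
- Report encounters, patients and deaths for each of the four hospital-periods, so that readers can see the balance.
- In Limitations, replace the claim that similar inclusion is ensured by a statement of how the switch date and the end of inclusion were actually set, in agreement with the Timeline.
- State as a limitation that random variation between hospital-periods cannot be estimated reliably from two hospitals and is not covered by the confidence interval.
- Optional: adjustment for age and sex, and standardised differences in place of baseline tests.

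Cost: analysis wording and a few lines of code. Hospital and date of visit are inherent in the data, and a patient identifier is needed anyway to apply the 30-day readmission rule. There is no burden on patients, and the loss of precision is about 0.5 % of the standard error under the 70:85 split.
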